#### Statistical analyses

Analyses will be done on both intention to treat (ITT) and per-protocol basis. The primary ITT analyses will be performed using linear mixed modelling (LMM) that adequately deals with missing at random data and the nested structure of repeated-measures data. LMMs with time, treatment and time-by-treatment interactions will be performed to test the effectiveness of the intervention in improving continuous primary and secondary outcomes of well-being, personal recovery, psychopathology, sef-compassion, positive relationships and dampening. Post-hoc independent t-tests with Holm-Bonferroni correction will be performed to test for significant between-group differences at all time-points. Based on estimated marginal means and corresponding standard errors from the LMM models, between-group standardized effect sizes will additionally be expressed as Cohen’s d with 95% confidence intervals (CI). Binary relapse data from the interviews will be analyzed with Kaplan Meyer survival estimates to compare the time to relapse and relapse rates between the intervention and control group. Differences in the proportion of relapsed patients and predictors of relapse will be additionally examined using generalized (binary) LMMs with post-hoc chi-square tests and relative risks (RR) with 95% CI to examine the significance and magnitude of differences at each follow-up point. Moderation and mediation analyses will be conducted to explore possible working mechanisms of the interventions. To calculate the cost-effectiveness of the intervention, quality adjusted life years (QALYs) will be taken into account as primary utility measure. QALYs will be calculated from the EQ-5D-5 L. The incremental cost-utility ratio (ICUR) will be calculated by dividing the difference in costs calculated from the TiC-P by the difference in the QALYs produced by the two groups. The ICUR is expressed as costs per QALY gained.

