### Intervention adjustments for euthymic BD patients

Since *“*This is your life*”* was not specifically developed for individuals with BD, we decided to customize the intervention content and delivery to the needs of this target group. The adjusted intervention is called “Living well with bipolar disorder”. We changed the mode of treatment delivery from individual self-help to group meetings (8–10 people per group), including eight sessions of 2 h conducted by a specially trained therapist. This setup is believed to give participants the possibility to share experiences with fellow patients and benefit from the presence of other group members.

Each week, a key positive psychology component will be covered and corresponding exercises will be introduced. Participants are also encouraged to keep training with those exercises at home (for 15–30 min per day). All intervention participants receive the self-help book *“*This is your life*”* [43], since several parts of the modules refer to chapters or exercises in the book. The adapted intervention consists of eight different modules covering different topics, such as positive emotions, positive relationships or personal goals. Homework differs depending on the module, but every week participants are encouraged to keep training with the exercises at home. Experiences with the homework is discussed at the beginning of each next session and possible obstacles or other benefits can be shared with the therapist and other group members. In case the module contains a collective exercise, a short debriefing session will take place immediately after the exercise, to discuss experienced benefits or difficulties. Every module contains a short break of 15 min. Every session is finished by a short conclusion in which the therapist summarizes the session and where uncertainties can be broached and questions can be asked.

In spring 2017, a formative user evaluation of *“*This is your life*”* was carried out to evaluate the original intervention contents. Five individuals with BD read and practiced a selection of the original exercises and rated them on a scale from 1 (*not at all*) to 5 (*extremely*), representing the relevance and usability of the exercises. Results of this group were used to further adapt and tailor the intervention to the needs of individuals with BD by taking into account the ratings of exercises, preferences of the patients and also their critical responses.

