### Statistical methods

#### Power calculation

The sample size calculation for this trial is conservatively based on the ability to detect at least a moderate effect of Cohen’s *d* = 0.60 in the post-hoc tests on the primary outcome (well-being) at post-intervention (T1). For a two-sided independent t-test with 80% power and *α* = 0.05, this requires 45 patients for both treatment groups. Taking a maximum drop-out rate of 20% into account, a total of 112 patients will need to be included for the per-protocol analysis.

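### Therapy-group clustering in the intervention arm is not allowed for in the power calculation or the post-hoc t-tests, so the stated 80% power is too high for any positive within-group correlation

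*Protocol article*

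**What the plan says.** Under *Intervention adjustments for euthymic BD patients*, the Protocol article changes delivery from individual self-help to "group meetings (8–10 people per group", with eight two-hour sessions led by a trained therapist. One stated reason is that participants should "benefit from the presence of other group members". Under *Study design*, the control arm receives care as usual only.

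Under *Power calculation*, the trial is sized to detect "at least a moderate effect of Cohen’s *d* = 0.60 in the post-hoc tests on the primary outcome (well-being" at the post-intervention measurement. The basis is: "For a two-sided independent t-test with 80% power" and a 5% significance level, "this requires 45 patients for both treatment groups". The only inflation is for attrition: "Taking a maximum drop-out rate of 20% into account, a total of 112 patients will need to be included".

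Under *Statistical analyses*, "LMMs with time, treatment and time-by-treatment interactions will be performed to test the effectiveness of the intervention". The reasons given for the mixed model are missing-at-random data and the nesting of repeated measures. Between-arm differences at each time point are then tested with Holm-Bonferroni corrected independent t-tests. No section names therapy group or therapist as a level, and the *Discussion* mentions group contact only as a non-specific factor.

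**The concern.** Members of one therapy group share a therapist, a centre, a calendar period and one another's company, and their mutual influence is an intended part of the treatment. Zero correlation within groups is therefore an assumption that needs a defence. Controls have no such grouping, so the variance of the mean is inflated in the intervention arm only.

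Two things are at stake. The first is the stated 80% power, which the article calls conservatively derived. The second is the standard error behind each between-arm test: if it leaves out the group component, p-values tend to be too small and intervals too narrow. With only a handful of groups, a test that does allow for them also loses degrees of freedom.

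**Working it through.** **Inputs from the article.** d = 0.60 (SD 1 on the standardised scale), two-sided 5%, 80% power, 45 evaluable per arm, 20% dropout, 112 in total, groups of 8–10 in the intervention arm only. **Assumed, because the article gives none:** within-group ICC of 0.01 / 0.05 / 0.10.

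**1. The plan's own figure.** For an independent t-test (noncentral t), 45 per arm gives power 0.804 and 44 per arm gives 0.795, so 45 is reproduced. Dropout: 90 / 0.8 = 112.5, in line with 112. At 0.804 there is no slack to absorb clustering.

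**2. Number of groups.** 112 / 2 = 56 are randomised to the intervention. 56 / 10 = 5.6 and 56 / 8 = 7, so about 6–7 groups. After dropout, the 45 evaluable patients are spread over them: m = 45 / 6 = 7.5 or 45 / 7 = 6.43.

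**3. Formulas.**
- Design effect, intervention arm only: DE = 1 + (m − 1) × ICC
- SE of the difference = √(DE/45 + 1/45); the unadjusted SE is √(2/45) = 0.2108
- Large-sample power = Φ(0.60/SE − 1.96)
- Type I error of one unadjusted 5% test ≈ 2 × [1 − Φ(1.96 × 0.2108/SE)]
- Small-sample power: noncentral t with Satterthwaite degrees of freedom, taking J − 1 for the J group means and 44 for controls

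Example, 6 groups, ICC 0.05: DE = 1 + 6.5 × 0.05 = 1.325; SE = √(2.325/45) = 0.2273; 0.60/0.2273 − 1.96 = 0.68; power = 0.752.

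**4. Results (6 groups / 7 groups).**

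| | ICC 0 | 0.01 | 0.05 | 0.10 |
|---|---|---|---|---|
| DE | 1 | 1.065 / 1.054 | 1.325 / 1.271 | 1.650 / 1.543 |
| SE | 0.2108 | 0.2142 / 0.2137 | 0.2273 / 0.2247 | 0.2427 / 0.2377 |
| Large-sample power | 0.812 | 0.800 / 0.802 | 0.752 / 0.761 | 0.696 / 0.714 |
| Type I error, one unadjusted t-test | 0.050 | 0.054 / 0.053 | 0.069 / 0.066 | 0.089 / 0.082 |
| Small-sample power | 0.768 / 0.775 | 0.752 / 0.762 | 0.692 / 0.713 | 0.625 / 0.657 |

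Simulations with 40,000 replicates agree to within about one percentage point. For the small-sample group-mean test they give power of about 76–77% at ICC 0, then 74–76%, 68–71% and 62–66%.

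**5. Separating the two losses.** The small-sample test already sits at 76–77% with no correlation at all. Of the fall from 80% to 68–71% at ICC 0.05, some 3–4 points are therefore degrees of freedom and the rest is correlation.

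**6. Detectable effect at 80% power.** (1.96 + 0.8416) × SE gives 0.637 / 0.629 at ICC 0.05 and 0.680 / 0.666 at ICC 0.10. Scaling the plan's own 0.60 by SE/0.2108 gives 0.647 / 0.639 and 0.691 / 0.677. Together these are about 0.63–0.65 and 0.67–0.69.

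**The case against.** *The model may yet include the group.* The article lists fixed terms and the reason for a mixed model, but does not set out the random-effects structure, which a condensed article can leave to the analysis plan. This stands as far as the mixed model goes: a reader might infer that it excludes the group level, but the text only fails to name it. It does not rescue the power statement or the independent t-tests, which the article does fix. If the analysis plan adds a group term, the stated 80% still fails for any positive ICC.

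*The size is unknown.* This also stands. At ICC 0.01 the loss is negligible and at zero there is none.

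*Centre correlation works the other way.* Randomisation is stratified by centre. Correlation that both arms of a centre share makes a test without a centre term conservative. In a simulation assuming six sites and a centre ICC of 0.05, the unadjusted type I error was 4.8% / 5.2% / 6.5% at group ICCs of 0.01 / 0.02 / 0.05. The net inflation thus depends on two unknown ICCs.

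*Stronger readings are not supported.* A reader might take the intervention arm to be worth only its handful of groups. At ICC 0.05 its effective size is 45/1.325 = 34 to 45/1.271 = 35 patients. A reader might also assume five full groups of nine and quote power as low as 58% and type I error near 10% at ICC 0.10. But 56 randomised patients in groups of 8–10 make 6–7 groups, thinned by dropout. Finally, the type I figures describe one uncorrected t-test. Neither the repeated-measures mixed model nor the Holm-corrected family was simulated, so they are not the error rate of the planned analysis.

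**Conclusion.** The point holds in a limited form. The article describes a partially nested design, sizes it as if all patients were independent, and tests time-point differences on the same basis. For any positive within-group ICC the 80% power is overstated, and a test that ignores therapy group tends to be anti-conservative.

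For an assumed ICC of 0.05, power for d = 0.60 is about 75–76% by large-sample calculation, or 68–71% with a small-sample test, part of which is lost degrees of freedom. The type I error of a single unadjusted test is about 6.5–6.9%. At 0.10 the figures are 70–71%, 62–66% and 8.1–8.9%. These rest on the assumed ICC, 45 evaluable patients per arm, 6–7 groups of near-equal size, equal total variance in both arms and no centre correlation.

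**What to change.** 1. Record a therapy-group identifier for every intervention participant.
2. Add to the repeated-measures mixed model a random effect for therapy group in the intervention arm only, with controls as singletons. Use Satterthwaite or Kenward-Roger degrees of freedom, and include centre, the randomisation stratum.
3. Take the time-point contrasts from that model, still Holm-corrected, in place of the independent t-tests.
4. Restate the power, or the detectable d, over a stated ICC range.

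Cost: one identifier, which should be simple to record, and one more variance term. Stated power becomes less favourable, intervals slightly wider, and a variance estimated from 6–7 groups will be imprecise, which should be acknowledged. No added enrolment is proposed; the lower power should be stated openly.

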**Method:**

The study concerns a pragmatic randomized multicenter trial. The principle objective of the study is to assess whether the positive psychology intervention offered to BD patients in remission in addition to usual care (CAU) is more effective than CAU. The study will include 112 participants randomized to either the experimental condition receiving the intervention in addition to CAU or the control condition receiving CAU. The study population are patients with BD I or II in the euthymic phase.

The inclusion criteria are 1) diagnosis of BD I or BD II, 2) between the ages of 18–65, 3) four or more supportive sessions in the last year, and 4) only residual depressive or manic symptoms. Patients are excluded if they are in a depressive or manic episode, have current addiction problems or have optimal levels of well-being. Measurements take place at baseline, post-intervention and follow-up 6 and 12 months from baseline. Outcomes of measures include positive well-being, personal recovery, psychopathology, self-compassion, positive relationships, dampening of positive affect and relapse.

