## Method

### Study design

A pragmatic, parallel-group randomized non-blinded multicenter trial is used to investigate the effectiveness of a multicomponent positive psychology intervention to improve well-being and personal recovery in patients with BD. Since the outcome in BD I and BD II disorder may be different, the sample will be stratified accordingly. Patients in the experimental condition receive “Living well with bipolar disorder” in addition to CAU. Participants in the control condition receive CAU only. Both participants in the control and experimental condition receive CAU according to the Dutch multidisciplinary guideline for BD [13], consisting mainly of self-monitoring of mood and supportive group sessions focusing on functional problems, and psychopharmacotherapy. The study duration is 12 months for each individual and includes five measurement points. Immediately prior to the start of the intervention a baseline measurement is completed (T0), 4 weeks after the start of the intervention a mid-treatment measurement takes place (T1) and immediately following the intervention a post measurement will be conducted (T2). In addition, two follow-up measures will be conducted, 6 months (T3) and 12 months after baseline (T4). Figure 1 shows the intended flow of participants (Additional file 1).

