### Randomization and treatment allocation

Randomization will be centrally conducted by the principal investigator using stratified (by center) block randomisation. For this purpose, randomization lists will be generated beforehand (one list for each participating treatment center) with an online tool (https://sealedenvelope.com/). The lists contain a random sequence of treatment allocations (i.e., participants are either allocated to the intervention or control condition according to the corresponding record) and are divided in blocks of allocations (20 allocations per block). By using blocks of allocations, 20 participants can be allocated to either the intervention or control condition after which the following block is used. This ensures that the group sessions in each center can start as soon as sufficient participants are randomized. The first participant included in the study is allocated according to the first record on the list, the second participant according to the second record on the list and so forth.

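### Time-point differences between arms are tested with independent t-tests that leave out baseline well-being and centre, although the LMM could supply adjusted contrasts from data already collected

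*Protocol article*

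**What the plan says.** Under Statistical analyses, the primary intention-to-treat analysis is an LMM with time, treatment and their interaction, chosen partly because it handles data missing at random. The next step is separate: "Post-hoc independent t-tests with Holm-Bonferroni correction will be performed to test for significant between-group differences at all time-points". Model output then enters as an addition, for Cohen's d and its confidence interval: "Based on estimated marginal means and corresponding standard errors from the LMM models".

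Under Power calculation, the trial is sized on those same tests, to detect "at least a moderate effect of Cohen’s *d* = 0.60 in the post-hoc tests on the primary outcome (well-being") after the intervention. The stated result is: "For a two-sided independent t-test with 80% power and *α* = 0.05, this requires 45 patients for both treatment groups". Drop-out is then allowed for: "Taking a maximum drop-out rate of 20% into account, a total of 112 patients will need to be included for the per-protocol analysis".

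On design factors, Randomization and treatment allocation describes allocation "using stratified (by center) block randomisation", with one list per centre. Study design states: "Since the outcome in BD I and BD II disorder may be different, the sample will be stratified accordingly". The analysis text names neither centre nor BD type. Study procedure shows that every participant has an MHC-SF score before allocation, because the screening score is not repeated at baseline. Table 2 lists the MHC-SF from T0 to T4.

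**The concern.** The plan picks a model for its handling of missing data and then hands the comparison on which the trial is sized to a test without that property. An independent t-test takes no covariates and uses whoever has a score at that visit. Three consequences follow.

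- **Precision.** A pre-randomisation MHC-SF score exists for everyone, and the t-test discards it. Centre, which restricts the randomisation, is discarded too.
- **Drop-out.** The plan allows for 20% drop-out, and the Discussion lists attrition as a likely source of bias. One arm attends eight group sessions with home exercises and the other continues usual care, so reasons for leaving could differ by arm.
- **Coherence.** P-values would come from t-tests and effect sizes from the model, on different sets of patients. A Cohen's d whose interval excludes zero could stand beside a non-significant p-value, or the reverse.

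In addition, testing at all time-points literally includes T0, where randomisation makes any difference a matter of chance, yet the test still enlarges the Holm family. BD type is described as relevant to outcome, but the randomisation section does not use it.

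**Working it through.** **Inputs from the article.** d = 0.60 (SD taken as 1), two-sided alpha 0.05, power 80%, 45 per arm, 20% drop-out, 112 in total. **Assumed, because the article does not give it:** the correlation rho between baseline and follow-up MHC-SF, taken over 0.3 to 0.7.

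**1. The plan's own figure.** With noncentrality d × √(n/2) and 2n − 2 degrees of freedom, n = 44 gives 79.5% power and n = 45 gives 80.4%. So 45 per arm is the answer for an unadjusted two-sample t-test at 0.05, with no baseline correlation in it. For the total, 90 / 0.8 = 112.5, against 112 stated; the difference is rounding.

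**2. Baseline adjustment.** Adjustment multiplies the residual variance by 1 − rho², so the effective effect size is 0.60 / √(1 − rho²). With 45 observed per arm and 87 degrees of freedom:

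| rho (assumed) | Variance factor | Effective d | Power, alpha 0.05 | n per arm for 80% |
|---|---|---|---|---|
| none used | 1.00 | 0.60 | 80.4% | 45 |
| 0.3 | 0.91 | 0.63 | 83.9% | 41 |
| 0.5 | 0.75 | 0.69 | 90.1% | 34 |
| 0.6 | 0.64 | 0.75 | 94.0% | 29 |
| 0.7 | 0.51 | 0.84 | 97.6% | 24 |

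**3. Holm threshold.** The MHC-SF has four post-baseline time-points. If these form the Holm family, its strictest step is 0.05 / 4 = 0.0125. Power for one comparison at that step is 61.7% unadjusted, 76.7% adjusted at rho 0.5 and 92.2% at rho 0.7. Adding T0 makes the step 0.05 / 5 = 0.01, and unadjusted power there is 58.5%. Later Holm steps are easier, so these are lower bounds.

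**4. Drop-out.** The simulation had 56 per arm, scores at T0, T1 and T2 with SD 1 and a common correlation, no true effect, and 4,000 replicates. In the differential case, drop-out after T1 depended on the T1 score in the intervention arm (logit −1.6 − 1.2 × score) and was unrelated to it in the control arm (logit −1.6). Overall drop-out was about 19%. In the equal case, the dependence applied in both arms and drop-out was about 22%.

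| Case | rho | t-test bias (SD) | t-test type I error | Likelihood-type estimate, bias (SD) |
|---|---|---|---|---|
| Differential | 0.5 | 0.113 | 8.0% | 0.007 |
| Differential | 0.7 | 0.154 | 11.4% | 0.002 |
| Equal | 0.5 | 0.001 | 5.8% | 0.001 |
| Equal | 0.7 | 0.001 | 4.8% | 0.001 |

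The likelihood-type estimate regresses T2 on T0 and T1 within arm and averages over everyone randomised. In the differential case, a baseline-adjusted regression on observed patients alone was still off by 0.063 SD (rho 0.5) or 0.047 SD (rho 0.7). Adjustment for baseline is therefore not enough; the contrast should come from the repeated-measures model, which also uses T1.

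**5. Stratification.** Study design has the sample stratified by BD I/II. The randomisation section has lists by centre only. These can be consistent only if the first refers to something other than allocation, such as the analysis, but the analysis text has no BD-type term.

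**The case against.** The strongest reply is that the t-tests are labelled post-hoc and that the stated primary analysis is the LMM. This stands in part. The time-by-treatment test keeps its missing-at-random validity and already uses T0. A reader might infer that the plan as a whole gives up that protection; the article does not support this.

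Second, the article does not say that the t-tests use raw scores, and they may have been meant as contrasts of model means. If so, the missing-data objection falls. But the text gives the model means a separate, additional use, and the power calculation is for a plain t-test. The precision point would survive: with complete data and categorical time, time-point means from a model with free baseline means in each arm equal the observed means.

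Third, the power gain is measured against a t-test, whereas the LMM interaction uses baseline. For a single change-from-baseline contrast the effective d is 0.60 / √(2(1 − rho)), which gives 80%, 88% and 95% at rho 0.5, 0.6 and 0.7. Against that benchmark, baseline adjustment gains about 10, 6 and 2 points. This is fair for the interaction, but the trial is sized on the t-test, and it meets its own 80% target at alpha 0.05. The loss is forgone precision, not an underpowered trial.

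Fourth, two stronger readings on drop-out do not hold. The t-tests are not valid only under missing completely at random, since drop-out acting equally in both arms gave no bias. Nor are they restricted to trial completers: each uses the patients observed at that visit. A bias of 0.21 SD can be derived (0.350 × 0.6), but only if the whole lowest fifth at T1 leaves one arm and nobody leaves the other.

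Fifth, covariance structure and similar model detail may be left to an analysis plan, and their absence is no criticism here.

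**Conclusion.** The point holds for the time-point tests and not for the primary LMM interaction test. The article fixes independent t-tests for the comparison that sizes the trial, although better use of the same data is available at no cost.

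The forgone power is about 3 to 17 percentage points (80% against 84% to 98%) over an assumed correlation of 0.3 to 0.7 at alpha 0.05. The possible bias is about 0.11 to 0.15 SD, with type I error of 8% to 11%, and arises only if drop-out depends on earlier scores differently by arm. The article gives no data on whether that will happen. Both the drop-out point and the possible conflict between p-values and effect sizes rest on the natural reading of the t-test sentence.

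The T0 test is a minor flaw. The two statements on BD type need reconciling whatever the analysis plan adds. A reader might conclude that BD type is certain to be neither balanced nor adjusted for. The article does not go that far, because it does not say at which stage the stratification applies.

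**What to change.** Replace the t-test sentence under Statistical analyses. State that treatment contrasts at each post-baseline time-point, with confidence intervals and Holm-adjusted p-values, come from the LMM, adjusted for baseline (as a covariate or through a common baseline mean for both arms), centre and BD type. Compute Cohen's d from the same contrasts, so that effect size and p-value agree. State that T0 is described and not tested, and remove it from the Holm family.

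Reconcile Study design with Randomization and treatment allocation. Either say that BD type is a stratum of the randomisation lists, or say that allocation is stratified by centre only and that BD type enters through the analysis.

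The analysis change costs wording only: baseline MHC-SF, centre and BD diagnosis are all recorded before allocation, and neither the sample size nor the visit schedule need change. The 45 per arm can stay as a conservative figure for the adjusted contrast at alpha 0.05.

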### Study procedure

Initial screening for participation will be performed by therapists working at the treatment centers. To assess symptom severity of possible participants, the Clinical Global Impression Scale – Bipolar (CGI-BP) is used. After possible participants sign the informed consent, the principal investigator contacts the patient and agrees on a time and date to conduct the additional screening. To verify the diagnosis of BD, the MINI international neuropsychiatric interview [37, 57] is used and to assess well-being, participants are asked to complete the Mental Health Continuum – Short Form (MHC-SF) [58]. Eligible participants are then asked to complete the first test battery at baseline. Since the MHC-SF has already been completed for screening reasons before, participants are not asked to complete it again at baseline. Baseline measurements should take approximately 40 min to complete. Afterwards, allocation of participants to the intervention or control group takes place.

The first intervention group will start approximately in fall 2018 and the last group will finish in fall 2019. Four weeks after the intervention begins (T1) and after the intervention has finished (T2), participants in the intervention and control condition are asked to fill out a test battery again. Six (T3) and 12 (T4) months after baseline, participants in the experimental and control group will be asked to complete the follow-up measures. We assume that completing the test battery takes approximately 35 min on average at each measurement point. At T4, participants will be approached for a semi-structured telephone interview with the goal to retrospectively assess relapse into mood episodes in the past 9 months. To perform the interviews, a guideline will be prepared and the interviews will be conducted by student assistants according to a fixed scheme. The trained student assistants are blind to the treatment condition of the participants. One interview will take approximately 30 min.

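### Read as written, the Holm-corrected t-tests include the pre-allocation baseline T0, which costs the post-intervention comparison of well-being about 3 to 6 points of power

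*Protocol article*

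**What the plan says.** The primary intention-to-treat analysis is a linear mixed model with time, treatment and their interaction. The Statistical analyses section then adds: "Post-hoc independent t-tests with Holm-Bonferroni correction will be performed to test for significant between-group differences at all time-points". It does not except baseline, list the members of the family, or say whether the correction is applied per outcome.

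The Study design section fixes the time points: "The study duration is 12 months for each individual and includes five measurement points". It names the first of them: "Immediately prior to the start of the intervention a baseline measurement is completed (T0"). Table 2 marks the MHC-SF, the well-being measure, at every point from T0 to T4. The Study procedure section says that the screening MHC-SF is not repeated at baseline, so the T0 value of the primary outcome is the screening value. After the baseline battery, it continues: "Afterwards, allocation of participants to the intervention or control group takes place".

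The Power calculation section ties the sample size to these same t-tests. The trial is sized to detect "at least a moderate effect of Cohen’s *d* = 0.60 in the post-hoc tests on the primary outcome (well-being") at post-intervention, and: "For a two-sided independent t-test with 80% power and *α* = 0.05, this requires 45 patients for both treatment groups".

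**The concern.** T0 is measured before anyone is allocated. In the randomised set the null hypothesis at T0 is therefore true by construction, and a test of it says nothing about the intervention. Holm nevertheless counts it. Each step divides 0.05 by the number of hypotheses still open, so a hypothesis that is almost never rejected holds every other threshold down.

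At stake is power for the post-intervention and follow-up comparisons. These t-tests are post-hoc to the mixed model, but they are the tests on which the trial was sized.

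**Working it through.** **Inputs from the protocol article.** Power calculation: two-sided t-test, alpha 0.05, d = 0.60, 45 per arm, 20% drop-out, 112 in total. Study design and Table 2: five time points for well-being, T0 to T4. Study procedure: T0 precedes allocation.

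**Assumptions not in the article.** The family is formed separately for each outcome. The correlation between any two time points is the same and lies between 0.4 and 0.75. The pattern of effects over time is as given in step 4.

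**1. The plan's own figure.** The noncentral-t solution for d = 0.60, alpha 0.05 and 80% power is 44.6, so 45 per arm; power at 45 is 80.4%. Drop-out: 90 / 0.80 = 112.5, which agrees with the stated 112 apart from rounding. The sample size reproduces.

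**2. Holm thresholds, 0.05 / (hypotheses still open).**

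| Family | Step 1 | Step 2 | Step 3 | Step 4 | Step 5 |
|---|---|---|---|---|---|
| With T0 (5 tests) | 0.0100 | 0.0125 | 0.0167 | 0.025 | 0.05 |
| Without T0 (4 tests) | 0.0125 | 0.0167 | 0.025 | 0.05 | – |

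While T0 is not rejected, the four real comparisons can use only the first four entries of the upper row, so the last is tested at 0.025 instead of 0.05.

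Example: real p-values 0.006, 0.009, 0.012 and 0.04, with T0 p = 0.60. With T0 in the family, the first three pass (0.006 ≤ 0.0100, 0.009 ≤ 0.0125, 0.012 ≤ 0.0167) and the fourth fails (0.04 > 0.025). Without T0, all four pass, the last because 0.04 ≤ 0.05.

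**3. Power of a single t-test at each threshold, 45 per arm, d = 0.60.** 58.6% at 0.0100; 61.7% at 0.0125; 65.8% at 0.0167; 71.4% at 0.025; 80.4% at 0.05. At the first step, T0 costs 61.7 − 58.6 = 3.1 points.

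**4. Power of the whole Holm procedure at T2.** Simulated patient-level data, t-tests with 45 per arm, 40,000 trials per setting, correlations 0.4, 0.6 and 0.75:

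| Assumed d at T1, T2, T3, T4 | With T0 | Without T0 | T0 falsely rejected |
|---|---|---|---|
| 0, 0.6, 0, 0 | 58–59% | about 62% | about 1% |
| 0.3, 0.6, 0.6, 0.6 | 62–63% | 67–68% | 2–3% |
| 0.6, 0.6, 0.6, 0.6 | 64–65% | 70–71% | 3% |

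The loss due to T0 is about 3 points in the first row, 4 to 5 in the second and about 6 in the third.

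**5. How much of the gap to 80.4% is due to T0.** With the effect at T2 only, Holm over four tests already takes power to about 62%, a loss of about 18 points, and T0 adds about 3. With d = 0.60 throughout, Holm over four tests costs about 9 to 10 points, and T0 adds about 6.

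**6. Family-wise error.** With no effect anywhere and correlations of 0 to 0.7, the chance of rejecting at least one post-baseline comparison was 3.1–3.9% with T0 and 3.7–4.9% without. Including T0 makes the procedure stricter, not looser.

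**7. Other outcomes (Table 2).** Personal recovery, social participation, depression, mania and anxiety are measured at T0, T2, T3 and T4, so their families would go from three to four. Self-compassion, positive relationships and dampening are measured at T0, T1 and T2, so theirs would go from two to three.

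**The case against.** **The authors may have meant post-baseline points only.** A condensed article does not list the Holm family, and a fuller plan could exclude T0. That the same section limits the relapse tests to follow-up points is weak evidence of a deliberate contrast, because relapse has no baseline value. This stands as a reason for modest weight. The sentence as written still includes T0, and it is a stated rule, not a detail left out.

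**The harm is limited.** The primary mixed model does not depend on these tests, and the error is on the conservative side. Both points stand. Against them, the sample size rests on these t-tests.

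**T0 equality is guaranteed only in the randomised set.** The article also plans per-protocol analyses and refers to them when it sets the sample size. In a per-protocol set, a baseline difference need not be pure chance. This qualifies the argument, but it does not turn a baseline comparison into a test of effectiveness.

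A reader might infer three stronger claims that the article does not support:

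- *T0 always blocks the full 5%.* It does not. If T0 gives p = 0.004 by chance alongside the real p-values in the example above, all five are rejected and the 0.04 comparison is tested at 0.05. This requires a false rejection at T0.
- *T0 costs 9 points, from 80.4% to 71.4%.* Those are powers of single tests at 0.05 and 0.025. Removing T0 does not restore 80.4%, because Holm over four comparisons still applies.
- *T1 should leave the family too.* That is a preference. Limiting the tests to T2, T3 and T4 would call for T3 and T4 tests of self-compassion, positive relationships and dampening, for which Table 2 schedules no data, and would drop one of their two post-baseline points. The Power calculation section also attaches the label T1 to post-intervention, whereas Study design and Table 2 make T1 mid-treatment and T2 post-intervention.

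**Conclusion.** The point holds as a matter of wording with a measurable but modest cost. As written, the correction spends part of alpha on a comparison made before allocation, and unless that comparison is falsely rejected, no real comparison is tested above 0.025. For well-being at T2, with 45 per arm and d = 0.60, the cost is about 3 points of power if the effect is at T2 only and about 6 if it is present at all four post-baseline points. These sizes rest on a family formed per outcome, correlations of 0.4 to 0.75 and the assumed effect patterns. The direction does not: adding a true null hypothesis to a Holm family cannot help the others. T0 explains only the smaller part of the shortfall from 80%.

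**What to change.** In Statistical analyses, replace the reference to all time points with *at all post-baseline time-points scheduled for each outcome*. Report T0 by arm descriptively, without a p-value. T1 can stay in the family for the outcomes measured then.

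In the same edit, reconcile the label for post-intervention, which is T1 in the Power calculation section and T2 in Study design and Table 2, so that it is clear which comparison the sample size refers to.

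The cost is one phrase and one label. No data collection, patient numbers or procedures change, and no test that bears on effectiveness is lost.
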